## Abstract

**Background:**

The COVID-19 pandemic is likely to increase anxiety and distress in young people worldwide. It is important to prioritize mental health during crisis events to mitigate the negative and often long-term effects of the crises on young people, families, and society. Mental health and well-being apps represent a scalable approach for improving psychological outcomes in young people and have potential to improve the equity of service access.

**Objective:**

The Whitu: 7 Ways in 7 Days well-being app was recently developed by our group to address the urgent need for innovative approaches to reach young New Zealanders who are struggling to cope with the COVID-19 pandemic. The aim of this study is twofold: to evaluate the acceptability of the prototype app and to examine the effectiveness of the refined app at improving mental and emotional well-being and reducing depression, anxiety, and stress in young people in New Zealand.

**Methods:**

A two-phase mixed methods study will be undertaken to achieve these aims. During the first phase, 20 young people aged 16-30 years (including those of Māori and Pacific ethnicity) will participate in a qualitative study to help refine the prototype app. During the second phase, 90 young people aged 16-30 years will participate in a randomized waitlist-controlled trial (RCT) to evaluate the efficacy of the refined Whitu app at 4 weeks and 3 months after baseline. Outcomes will be evaluated using validated web-based questionnaires at baseline, 4 weeks, and 3 months.

**Results:**

The study received ethics approval in May 2020, and recruitment for the focus groups commenced in June 2020. Recruitment for the RCT is expected to commence in October 2020. Participants for both study phases will be recruited via social media and web-based communities. Data collection for the RCT is expected to be completed by January 2021, and analyses are expected to be completed by March 2021. Linear mixed modelling will be used to determine between-group differences in psychological outcomes.

**Conclusions:**

There is an urgent need to develop culturally appropriate, scalable mental health interventions to address the psychological consequences of the COVID-19 pandemic. In this study, we will develop and test an evidence-based well-being app that, if effective, can be made available to all young people in New Zealand and internationally.

**Trial Registration:**

Australian New Zealand Clinical Trials Registry (ACTRN12620000516987); https://www.anzctr.org.au/Trial/Registration/TrialReview.aspx?id=379597.

**International Registered Report Identifier (IRRID):**

PRR1-10.2196/23716

## Introduction

### Background and Rationale

Prior to the COVID-19 pandemic, New Zealand young people, especially Māori (indigenous New Zealanders) and those of Pacific ethnicity, were already experiencing high rates of psychological distress and mental illness [1-4]. Crisis events, including pandemics, can result in significant mental health consequences both during and after the crisis, including increases in depression, anxiety, posttraumatic stress disorder, and suicide [5-8]. In the longer term, these problems can leave a damaging societal footprint, with markers such as increased exclusion or disengagement from education, academic underachievement, and unemployment [9]. It is likely that recent local stressors related to rapid lockdown, physical isolation, disrupted academic routines, and families’ financial insecurity will exacerbate pre-existing mental health issues and generate new ones, especially anxiety and depression in young people [10-12]. To minimize the immediate and future adverse psychological and social consequences of the pandemic, young people urgently need support to develop skills to maintain their well-being, address mental health issues early, and continue to build resilience during the coming months.

Over the past 20 years, rapidly evolving mobile technology has fostered the development of a range of eHealth interventions, including those designed to improve mental health, such as mental health apps [13]. Evidence has suggested that eHealth interventions for mental health conditions, such as depressive disorders, can be as effective as face-to-face therapies [14,15]. Acknowledging the effectiveness of eHealth interventions for people of all ages and the relatively good smartphone access in most developed countries, international organizations such as the Lancet Global Mental Health Group have highlighted the role of eHealth interventions in preventing and addressing common mental health issues in adults, young people, and children [16]. Key purported advantages of eHealth interventions include their flexibility of use, cost-effectiveness, and potential to increase equity of service access and reduce stigma [17]. These advantages are reflected by the willingness of people, especially “digital natives,” to use eHealth interventions [18].

Alongside these technological developments, evidence has been increasing that specific therapeutic modalities enhance mental health and well-being in children and young people and that these can effectively be delivered as eHealth interventions, such as cognitive behavioral therapy (CBT) [13,19] and psychoeducation [20]. Awareness is also growing that self-empowerment of well-being can improve the quality of care and outcomes for people experiencing mental health problems [21,22], and it has been suggested that interventions should equally aim to enhance well-being and attempt to reduce distress [23]. Digital interventions such as apps must be user-centered to produce the best outcomes for people [24,25]. Well-designed interventions can cost less to produce and lead to greater user satisfaction and content completion [25]. There are currently no evidence-based well-being apps specifically tailored for young people living in New Zealand to help them manage their psychological well-being during the COVID-19 pandemic.

This project has been designed to address the psychological needs of New Zealand young people aged 16-30 years, especially those of Māori and Pacific ethnicity, during the COVID-19 pandemic. At the start of the pandemic (in March 2020), a preliminary prototype app called Whitu: 7 Ways in 7 Days was rapidly developed by our group in response to our clinical concern for this cohort. *Whitu* is the Māori word for “seven,” and as its name suggests, the app includes seven modules that can be completed within a week to learn evidence-based coping skills based on our previous work using CBT, psychoeducation, and positive psychology techniques [26-28]. The seven modules and skills included in the app have all previously demonstrated efficacy for young people and as individual eHealth interventions: (1) identifying and rating emotions [20], (2) relaxation [19], (3) self-compassion [29,30], (4) gratitude [31,32], (5) staying connected [33,34], (6) physical care [35,36], and (7) goal setting [37,38].

The specific objectives of the current project are to refine the prototype evidence-based app for improving the well-being and mental health of New Zealand young people aged 16-30 years; ensure broad end-user and cultural acceptability of the app, particularly to Māori and Pacific young people; and demonstrate the preliminary clinical effectiveness of the app via objective outcome measurement during a randomized waitlist-controlled trial (RCT).

## Methods

### Study Design

A two-phase, mixed-methods design will be employed. During the first phase, a qualitative study will be conducted with users of the prototype app, and the app will be refined on the basis of their feedback. During the second phase, an RCT will be conducted according to CONSORT (Consolidated Standards of Reporting Trials) guidelines [39].

### Phase 1: Qualitative Study

#### Participants

Approximately 20 young people from New Zealand aged between 16 and 30 years will be recruited during June to August 2020 from web-based communities and groups (eg, Facebook, Instagram, Tuakana-teina/Māori student mentorship programs) to help refine the prototype app design and content. A series of five focus groups will be conducted to collect feedback, with three to six people per group. We will recruit at least ten Māori and Pacific young people to ensure the app appeals to these audiences and is culturally appropriate.

#### Procedures

Recruitment will be conducted and informed consent will be obtained on the internet over a secure website, Research Electronic Data Capture (REDCap) [40,41]. Prior to attending the focus groups, participants will be asked to provide demographic variables, including age, sex, ethnicity, pre-existing mental health conditions, and experience of using well-being and mental health apps, via self-report questionnaires on REDCap. Participants will also be asked to download and use the prototype app for approximately one week prior to attending the focus groups.

The focus groups will last between 1.5 and 2 hours and will be conducted via Zoom, with two focus groups including only Māori and Pacific young people. To ensure culturally appropriate processes and participant comfort, these focus groups will be facilitated by our Māori and Pacific researchers ([name]). Ideas for integrating wider Māori and Pacific views of mental well-being will be explored, and the cultural appropriateness of Māori and Pacific design motifs will be assessed.

During the focus groups, participants will provide audio-recorded feedback on their experiences of using all seven modules. All participants will receive a voucher for NZ$40 (US $26.36) for attending the focus groups.

#### Data Analysis

Participants’ qualitative data will be audio-recorded and transcribed. The transcribed data will be analyzed using directed content analysis [42], a qualitative approach that is well suited for focus groups or interviews where predetermined concepts or categories are examined (eg, usability and acceptability of the different functions and content of the app). The coding scheme will be partly based on the user version of the Mobile Application Rating Scale (uMARS) [43] domains (Engagement, Functionality, Aesthetics, and Information), and the cultural acceptability of the scheme will also be explored by [name]. The data will be coded and analyzed independently by at least two members of the research team. Any discrepancies in coding will be resolved by consulting the wider research team.

### Phase 2: Randomized Waitlist-Controlled Trial

#### Participants

Participants will be New Zealand residents between the ages of 16 and 30 years. Recruitment is expected to commence in October 2020 via social media (Facebook, Instagram) as well as on other New Zealand–based web-based communities. Young people who participated in phase 1 (qualitative study) will not be eligible to participate in the RCT. Participants will receive a NZ$40 voucher (US $26.36) for taking part in the RCT. Participants who are currently receiving mental health treatment (including using a mental health app) are not eligible to participate.

#### Procedures

Participants will be recruited from web-based communities (eg, social media) by an advertisement or flyer with a link to the REDCap site. On REDCap, interested participants will be screened for eligibility. If eligible, they can read and download the Participant Information Sheet, provide web-based consent, and complete the baseline questionnaires once they have consented. Once participants have consented and completed the baseline questionnaires, they will be randomized into either the intervention group (Whitu app) or wait-list control group. Randomization will occur using REDCap’s randomization module. Participants and research staff will not be blinded to treatment allocation. The wait-list control group will receive the app 3 months after the initial app group. Figure 1 shows the CONSORT flow diagram.

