**Figure 1 figure1:**
[figure not shown]
CONSORT (Consolidated Standards of Reporting Trials) flow diagram of participant recruitment, randomization, and attrition.

After randomization, the wait-list group will be informed that they are in the wait-list control group on REDCap. The intervention group will be shown a link and instructions on how to download the Whitu app on REDCap. During the first four weeks, participants in the intervention group will receive 2 emails reminding them to complete the app modules and an SMS text message asking them to confirm whether they have been able to download the app. Four weeks after completing the baseline questionnaires, participants in both groups will receive an email with a link to the first follow-up questionnaire on REDCap. Three months after baseline, both groups will receive an email with the link to the final follow-up assessment. After the wait-list control group completes the 3-month assessment, REDCap will send each group member an automated email with instructions on how to download the Whitu app. We will not follow up with the wait-list control group after they receive the app at the 3-month time-point.

All participant outcome data (eg, demographic data and psychological outcomes) will be collected via REDCap. We will not collect any information via the app, and any user input (eg, first name, responses to exercises) will only be stored locally on the user’s device. Only the Principal Investigators and research assistants ([name]) will have access to the participant data collected over REDCap. When the data are exported from REDCap, all data will be deidentified and stored separately from the participants’ information.

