### Power Calculation

A previous study of a web-based positive psychology intervention for mildly depressed adults [44] found a between-group improvement in well-being (effect size of *f*=0.155) using the World Health Organization-Five Well-Being Index (WHO-5) [45]. Using G*Power [46], we calculated that the minimum required sample size to detect an effect size of *f*=0.155 using a mixed analysis of variance (ANOVA) including within-subject (3 time points) and between-subject (2 groups) effects with 90% power and at a 2-sided 5% significance level was 90 participants (45 per treatment arm). To ensure cultural acceptability, we will aim to recruit at least 40% Māori and Pacific young people (n=36).

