##### 6. User Engagement

This outcome will be assessed via two subscales (App Subjective Quality, Perceived Impact) of the end-user version of the uMARS [65]. The uMARS is a self-report scale designed to assess the quality of health apps. The Subjective Quality score for the app is derived from four items that determine user experience (eg, “Would you recommend this app to people who might benefit from it?”). These items are scored on a 5-point Likert scale ranging from 1 to 5; however, each has different anchors. Scores from this subscale can be reported individually or as a mean total. The Perceived Impact score consists of six items that measure the impact of using the app on knowledge, attitudes, and intentions. The six items are reported as individual items and measured on a Likert scale ranging from 1 to 5 (1, strongly disagree; 5, strongly agree). The uMARS demonstrates good internal reliability overall (α=.90), and the two subscales demonstrate good to moderate reliability (α=.71 and .80) [43]. The scale also contains an open-ended question that asks: “Do you have any further comments about the app?”

In addition to the uMARS, participants will also be asked the following questions about their use of the Whitu app: (1) How many modules did you complete? (2) On how many days did you use the app? (3) What module was the most useful? Why? (4) What did you like about the app? (5) How can we make the app better for young people in the future? and (7) Did you experience any technical difficulties with the app? If yes, what happened?

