#### Hypotheses and Statistical Analyses

It is predicted that the Whitu app group will demonstrate improved well-being (increased emotional and mental well-being), increased self-compassion, and improved sleep at 4-week and 3-month follow-up compared to the wait-list control group. We also hypothesize that the Whitu app group will demonstrate decreased stress, depression, and anxiety at 4-week and 3-month follow-up compared to the wait-list control group.

Data will be analyzed in SPSS (IBM Corporation) or SAS (SAS Institute). Prior to any data analysis, the data will be tested for violations of statistical assumptions and screened for errors and outliers. If parametric assumptions are not met due to nonnormality, transformations or nonparametric tests will be used. Pearson correlations (or Spearman ρ if nonnormal) will be used to explore the relationships between the outcome measures and demographic characteristics and other psychosocial factors. ANOVAs or Kruskal-Wallis tests (if nonnormal) will be used to explore associations between categorical variables and outcome measures. Linear mixed models will be used to determine whether changes in psychological outcomes are the result of the interaction between the intervention group and time, with post-hoc tests to assess pairwise comparisons of groups at each time point and within-group changes over time. Linear mixed models also allow for missing data, as they enable all participants with baseline data to be included in the analysis. We will also examine possible 3-way interactions with age, sex, or ethnicity (eg, age*group*time). Means, SDs, and CIs will be presented with the analysis. Data will be subjected to both intention-to-treat and per-protocol analyses. Per-protocol analyses will include participants who report completing all seven modules. Study results will be disseminated through peer-reviewed journals and conferences.

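### As the plan is written, outlier screening and the data-driven choice of method can be done knowing the arm; masking the arm at export is a cheap, modest improvement

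*Protocol article*

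**What the plan says.** - **Blinding** (Protocol article, Phase 2, Procedures): "Participants and research staff will not be blinded to treatment allocation". The sentence covers all research staff and carves out no data-handling or analysis role.
- **Capture** (same section, text after Figure 1): "All participant outcome data (eg, demographic data and psychological outcomes) will be collected via REDCap". Participants answer web questionnaires and no staff member rates an outcome.
- **Access** (same place): only the principal investigators and research assistants "will have access to the participant data collected over REDCap".
- **Export** (same place): "When the data are exported from REDCap, all data will be deidentified and stored separately from the participants’ information". The arm variable is not mentioned.
- **Screening** (Hypotheses and Statistical Analyses): before analysis "the data will be tested for violations of statistical assumptions and screened for errors and outliers".
- **Choice of method** (same section): "If parametric assumptions are not met due to nonnormality, transformations or nonparametric tests will be used".
- **Items that reveal the arm** (Outcome Measures, User Engagement): besides the app-rating subscales, "participants will also be asked the following questions about their use of the Whitu app". The wait-list arm has no app until after its 3-month assessment. The per-protocol set is defined by reported completion of all seven modules.

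**The concern.** Participants cannot be blinded to receiving an app. The person who cleans the questionnaire data can be, and the article gives no reason for leaving that step open. Read together, the statements declare the only people named with data access to be unblinded, and they call for two judgements on the data before the comparison is made: which values are outliers, and whether the distribution calls for another method. The app was developed by the same group.

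The scales have fixed responses and bounded totals: WHO-5 0 to 100, SWEMWBS 7 to 35, CES-D 0 to 60, sleep quality 0 to 10. An extreme total inside the range is therefore a possible answer, often from a participant who is doing badly, and is not in itself a data error. If such values were set aside more readily in one arm than the other, the group comparison would shift in a way that randomization does not protect against.

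**Working it through.** **1. The plan's own figure.** The Power Calculation gives 90 participants (45 per arm) as the "minimum required sample size to detect an effect size of *f*=0.155", with 90% power, two-sided 5%, 2 groups and 3 time points. For the group-by-time interaction, the noncentrality is λ = f²·N·m/(1−ρ). The article does not state the correlation or the sphericity correction; I assume ρ = 0.5 and ε = 1.

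- λ = 0.155² × 90 × 3 / 0.5 = 0.024025 × 540 = 12.97
- df1 = (2−1)(3−1) = 2; df2 = (90−2)(3−1) = 176
- Power = 90.2%, and the smallest N reaching 90% is 90.

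The stated size reproduces. At other assumed correlations N would be 126 (ρ = 0.3), 108 (0.4), 72 (0.6) or 56 (0.7). The test of the between-group main effect would need 294, so that is not the variant used. Masking the arm changes none of these figures.

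**2. What knowledge of the arm could do.** This is an illustration under no true effect: 45 standard normal scores per arm, a two-sample t-test at one time point, 40,000 runs per setting, and outliers flagged by their distance from the pooled mean in pooled SDs. The article states no cutoff, so three are assumed.

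- *Arm-blind*: every flagged value is removed, in both arms and both directions.
- *Arm-aware, worst case*: only low flagged values are removed from the app arm and only high ones from the control arm.
- *Arm-aware, half*: each of those unfavourable values is removed with probability one half.

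| Cutoff | Arm-blind: type I error, bias | Arm-aware, worst case: type I error, bias | Arm-aware, half: type I error, bias |
|---|---|---|---|
| 2 SD | 4.9%, about 0 | 7.7%, 0.105 SD | 5.6%, 0.053 SD |
| 2.5 SD | 5.0%, about 0 | 5.3%, 0.032 SD | 4.9%, 0.017 SD |
| 3 SD | 4.7%, about 0 | 4.9%, 0.007 SD | 5.1%, 0.003 SD |

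In the worst case the mean number of values removed per trial is about 2.0 at 2 SD, 0.5 at 2.5 SD and 0.1 at 3 SD.

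**3. Hand check.** The standard error of the difference is √(2/45) = 0.211 SD. A bias of 0.105 SD is 0.105/0.211 = 0.50 standard errors, so two-sided rejection is about P(Z > 1.46) + P(Z < −2.46) = 0.072 + 0.007 = 7.9%, close to the simulated 7.7%. A bias of 0.032 SD is 0.15 standard errors and gives about 0.035 + 0.017 = 5.2%, against 5.3%.

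Arm-blind removal discards more values than arm-aware removal (about 3.9 against 2.0 at 2 SD) and still gives no bias. The bias comes from knowing the arm, not from the screening.

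**The case against.** **The screener is not named.** The screening sentence is passive, the unblinding sentence does not mention data cleaning, and the export sentence does not say who handles the exported file. A reader might infer that staff who know the arm will certainly do the screening. The article does not say so. It leaves this open, and a blanket unblinding statement makes it the natural reading. This part of the objection stands.

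**Screened is not removed.** A reader might also infer a breach of intention-to-treat. No deletion is planned in the text. The stated response to nonnormality is transformation or nonparametric tests, and the mixed model is meant to keep everyone with baseline data. A conflict would arise only if in-range values were in fact dropped.

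**Larger effects are easy to produce.** Deleting the 1, 2 or 3 lowest app-arm scores by rank shifts the difference by 0.05, 0.09 or 0.13 SD and raises false positives favouring the app from 2.4% to 4.4%, 6.9% or 10.2%. That is selective deletion rather than outlier screening. Among 45 normal scores the second lowest lies beyond −2 SD in only 27% of samples and the third in 8%; beyond −2.5 SD the figures are 3% and 0.3%. Nor should these shifts be expressed as shares of d = 2 × 0.155 = 0.31, because N = 90 reproduces for the interaction and not for a between-group difference.

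**Outlier rules belong in an SAP.** This is true, and their absence is not the finding. What remains is the affirmative statement that leaves all research staff unblinded where part of the work could be masked.

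**A larger bias remains.** Participants who know their arm report every efficacy outcome. Masking the cleaning does not touch that.

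**Conclusion.** The point holds in a limited form. The article makes a stated choice to leave all research staff unblinded, and as written this lets outlier judgements and the choice of method be made knowing the arm, although nothing in the design requires it. The possible distortion depends on the cutoff: in the worst case about 0.1 SD of bias and 7.7% type I error at 2 SD, 0.03 SD and 5.3% at 2.5 SD, and negligible at 3 SD. With masked screening the bias is essentially zero.

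These sizes assume normal scores, full follow-up of 45 per arm, a single-time t-test instead of the planned group-by-time mixed model, and actual removal of flagged values, which the article does not announce. Bounded scales may limit extremes further. The effect of choosing a transformation or nonparametric test with knowledge of the arm was not quantified. Masking is a worthwhile, low-cost improvement, and its absence does not by itself undermine the trial.

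**What to change.** **Phase 2, Procedures**
- Limit the unblinding statement to participants and the staff who run the trial.
- State that the de-identified export carries a neutral arm code, with the key held by an existing team member who does not clean the data.
- Hold back from the cleaning file everything that would reveal the arm: the user-engagement items (app rating and app-use questions, including free text) and the seven-module per-protocol flag.

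**Hypotheses and Statistical Analyses**
- State that error and outlier screening, assumption checks and any resulting choice of transformation or test are completed and locked before the arm is attached.
- State that in-range questionnaire values are kept unaltered in the intention-to-treat analysis, and that any outlier-excluded analysis is a sensitivity analysis with one rule for both arms.

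**Cost.** One small data-handling step, a code-holder from within the team, a few sentences of text, and a per-protocol analysis that waits until unmasking. That is cheap, though not free. The sample size of 90 and all participant procedures stay as they are. The report should still acknowledge the bias from unblinded self-report, which this change does not reduce.
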